**6.6 Data processing**

Paper based and electronic data entry will be used. RRAs enter locally collected data to the database in the CHs for screening and randomisation purposes. Paper based CRF data will be delivered securely to the Trial Office for data entry. Staff in the Trial Office work closely with local RRAs to ensure the data are as complete and accurate as possible.

## 7. SAFETY

**7.1 Standard definitions**

An **adverse event** (AE) is any untoward medical event affecting a clinical trial participant. Each initial AE is considered for severity, causality or expectedness and may be reclassified as a serious adverse event based on prevailing circumstances.

A **serious adverse event** (SAE), is any AE, that:

- results in death;
- is life threatening (i.e. the subject was at risk of death at the time of the event; it does not refer to an event which hypothetically might have caused death if it were more severe);
- requires hospitalisation or prolongation of existing hospitalisation;
- results in persistent or significant disability or incapacity;
- is otherwise considered medically significant by the investigator.

***7.2 Trial specific considerations***

In this trial, all AEs occurring during an electrical stimulation (treatment/sham) session, or while equipment is attached to the resident’s leg, or during data collection periods are recorded eg during questionnaire completion, interviews or 24-hour pad collections (see definitions below). Given the previous established safety profile of the TPTNS, serious related AEs are not anticipated in this low-risk trial. However, any serious related AEs that do occur will be recorded as such.

Hospitalisations for elective treatment of a pre-existing condition are not considered as an AE or SAE. Complications occurring during such hospitalisation are also not AEs or SAEs.

Falls, fractures, UTIs, emergency admissions to hospital in 6-month period prior to the resident’s participation in the ELECTRIC trial are recorded at study baseline. Falls, fractures and emergency admissions to hospital are not considered as related AEs/SAEs during the trial period unless they occur during a treatment session or during the measurement of study outcomes. Symptomatic UTIs treated with antimicrobials occurring at any time during the resident’s 18-week participation period, are considered to be AEs/SAEs.

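### Section 7.2 denies AE and SAE status to every complication of an elective admission, contradicting its own rules on treated UTIs and serious related events

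*Protocol*

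**What the plan says.** Section 7.1 gives standard definitions. An AE "is any untoward medical event affecting a clinical trial participant". Among the criteria that make an AE serious are that it "results in death" or "requires hospitalisation or prolongation of existing hospitalisation". Neither definition makes an exception for events that arise in hospital.

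Section 7.2 then sets trial-specific rules:

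- **General window.** Recording covers "all AEs occurring during an electrical stimulation (treatment/sham) session, or while equipment is attached", and also events during data collection.
- **Serious related events.** The section says that "any serious related AEs that do occur will be recorded as such". No time window or setting is attached.
- **Elective admissions.** "Hospitalisations for elective treatment of a pre-existing condition are not considered as an AE or SAE".
- **Complications of those admissions.** "Complications occurring during such hospitalisation are also not AEs or SAEs".
- **UTIs.** "Symptomatic UTIs treated with antimicrobials occurring at any time during the" resident's 18 weeks in the trial count as AEs/SAEs. No setting is excluded.

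Section 7.3.1 makes section 7.2 the operative filter: only events that meet its criteria are recorded, from consent to last follow-up. Seriousness, relatedness and expectedness are then evaluated under 7.3.3, with notification and reporting under 7.3.4 and 7.3.5.

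**The concern.** Exempting a planned admission is common and sensible, because the admission is not a new untoward event. Exempting whatever goes wrong during it is a different rule, and it turns on where the resident happens to be. The sentence carves out nothing for UTIs, seriousness or relatedness, so it overlaps with two categories that the same section says are to be counted. No rule of precedence is given.

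AE status is the entry point to the whole safety process. An event declared not to be an AE is never put through the relatedness assessment in 7.3.3. It therefore cannot reach the 24-hour sponsor notification in 7.3.4 or the 15-day report to the ethics committee in 7.3.5. At stake are complete and consistent capture of the events that the trial chose to count, and a relatedness question that stays open until someone has answered it.

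**Working it through.** The protocol states no figure on this point, so the check sets the rules side by side for each kind of event that could arise around an elective stay.

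| Event | Complications sentence (7.2) | Other rules | Result |
|---|---|---|---|
| The planned admission itself | Not addressed | Elective-admission sentence (7.2): not an AE or SAE | Consistent within 7.2; not disputed |
| Treated symptomatic UTI acquired during the stay, within the 18 weeks | Not an AE or SAE | UTI rule (7.2): AE/SAE | Direct contradiction |
| Serious event related to research procedures, arising during the stay | Not an AE or SAE | Serious-related rule (7.2): recorded | Direct contradiction |
| Unrelated complication, not a UTI, that prolongs the stay or is fatal | Not an AE or SAE | 7.1: an SAE; 7.2 window: not recorded | Labels disagree, but the event goes unrecorded either way |
| Non-serious complication, not a UTI, outside sessions and data collection | Not an AE or SAE | 7.1: an AE; 7.2 window: not recorded | Labels disagree, but the event goes unrecorded either way |

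Rows two and three are the point. In both, one sentence of 7.2 brings the event in and another puts it out.

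Row four shows why the sentence also sits badly with 7.1. The criterion about prolonging an existing hospitalisation describes a complication in someone already admitted. Section 7.1 calls that serious, while 7.2 says it is not even an AE.

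The last two rows set the limit. Removing the sentence would not bring those events into the record, because the general window in 7.2 already leaves them out.

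**Size.** The protocol gives neither an elective admission rate nor a rate of UTI during such stays, so the number of affected events cannot be derived. As an illustration only, assume that 5% to 10% of the 500 residents have an elective admission during the trial, that 5% to 10% of those acquire a treated UTI, and that every such UTI is then dropped:

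- low: 500 × 0.05 × 0.05 = 1.25
- high: 500 × 0.10 × 0.10 = 5

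That is roughly one to five UTIs across both arms combined. All three assumptions come from outside the protocol. Serious related events would be additional, but section 7.2 does not anticipate any.

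**The case against.** The strongest reply is that section 7.2 is headed as trial-specific and section 7.3.1 makes it the filter, so it may narrow the general definitions in 7.1. That stands. A trial may limit what it records, and tension with 7.1 alone would be a matter of loose wording. It does not answer the conflict inside 7.2, where the narrowing sentence meets two rules of equal standing.

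A second reply is that the UTI rule is specific and emphatic, so a site could reasonably follow it and record the event. That is possible, and it means that loss of these UTIs is not certain. But the complications sentence is just as categorical, and another site could follow that one. Inconsistent classification is itself the problem.

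Four stronger readings are tempting, and the protocol does not support them:

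- **The sentence is what keeps fatal or life-threatening complications from being assessed.** For unrelated complications this is wrong, because the general window in 7.2 excludes them with or without it. Only serious events related to research procedures are affected.
- **Treated UTI is the only event captured throughout the 18 weeks.** It is not. The rule on serious related AEs has no time window either.
- **Losing UTIs undermines the check that less leakage is not due to retained urine.** Section 6.1 addresses that directly with post-void residual volume, which Table 1 schedules at baseline and at 6, 12 and 18 weeks.
- **The comparison between arms is biased.** The rule is the same in both arms, section 4.7 describes sham control to blind residents and relatives, and section 10.1 plans descriptive safety summaries. Nothing in the protocol shows a differential effect.

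**Conclusion.** The point holds in a limited form. Section 7.2 contradicts itself for two kinds of event arising during an elective stay: treated symptomatic UTIs and serious related events. Followed literally, the complications sentence removes them before relatedness is considered; followed selectively, it lets sites differ.

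The consequence is a small under-count of unknown size and inconsistent classification. The count of one to five UTIs is illustrative and rests on assumed rates. The contradiction itself rests on the text alone and needs no assumption. The sentence is worth correcting because the remedy is short and cheap and the events concerned are ones that the protocol has already decided to count.

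**What to change.** Reconcile the passages in section 7.2. Keep the exemption for the planned admission, and either delete the complications sentence or replace it with wording such as:

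*The planned admission itself is not an AE; complications arising during it are assessed and recorded by the same section 7.2 criteria as any other event, including the rules for treated UTIs and serious related AEs.*

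This leaves the existing recording window as it is and does not widen capture to unrelated complications of elective treatment. The cost is a one-sentence amendment and a few extra event forms.

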**3.1 Intervention being evaluated**

***Transcutaneous posterior tibial nerve stimulation*** (TPTNS) is a form of peripheral neuromodulation. The full 12 session programme (a total of 6 hours) is delivered in 30 minute sessions twice weekly over a 6-week period. The tibial nerve, which lies immediately posterior to the medial malleolus is stimulated electrically using a portable TENS machine and two surface electrodes. The cathode electrode is positioned behind the medial malleolus and the anode 10cm cephalad to it. Standardised stimulation parameters are applied of 10 Hz frequency, 200µs-1 pulse width in continuous mode and stimulation intensity (mA-1) is adjusted on a session-by-session basis according to individual resident comfort levels.

Although the exact mechanism of action has yet to be fully understood, TPTNS is believed to restore the balance between excitatory and inhibitory bladder functioning by modulating the signal traffic to and from the bladder through the sacral plexus47. It is hypothesised that stimulating afferent sacral nerves in the lower extremities increases the inhibitory stimuli to the efferent pelvic nerve, suppresses bladder afferent nerve activity, reduces detrusor contractility and increases bladder capacity48 and by these means TPTNS reduces the sensation of urgency and the frequency of micturition demanded, thus enabling improved bladder control. These mechanisms may also reduce the volume of urine retained in the bladder after voiding1, 29. For the CH population who wear absorbent pads because of mixed/urgency incontinence, TPTNS may reduce the sudden urge to urinate and frequency of voiding, allowing residents more time to reach the toilet, which in turn will enable more appropriate use of the toilet, generating respect and enhancing the person’s dignity.

As a potentially therapeutic modality TPTNS occupies a unique position in the CH care pathway for UI as it provides active treatment of the mixed/urge UI condition without requiring any active contribution by the resident, thus unusually, it is as likely to be of benefit to those with cognitive impairment as those without, and has been shown to be safe and not associated with any severe or limiting adverse effects.

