## 6. DATA COLLECTION AND PROCESSING

#### *6.1 Measuring outcomes*

Outcomes are measured at 6, 12 and 18 weeks post randomisation. The primary outcome is the volume of UI leaked in 24 hours at 6 weeks post randomisation, as measured by a 24-hour pad weight test (PWT)37. Pad weight tests at 12 and 18 weeks measure the sustainability of any effect. The test is based on the premise that 1g fluid weight = 1 ml urine and is thus an objective measure of urine leakage. The PWT involves the resident emptying their bladder, applying a clean, dry pad at an agreed set time and retaining all pads used between this time and 24 hours later. To maintain the moisture in the removed pads and prevent evaporation all collected pads are individually sealed in a small plastic bag and then placed in a larger re-sealable bag, which is weighed on site by the RRA after the 24-hour collection ends. The dry weight of the equivalent pads to those collected is deducted from the total weight to provide the 24-hour volume of UI leaked.

Secondary OCM include the *number of pads used in 24 hours*, which may be expected to reduce if TPTNS is effective in reducing volume of UI and will be reflected in the economic evaluation*.*

*Post void residual urine volume* (PVRU) is measured using a non-invasive portable ultrasound bladder scanner. Our pilot study conducted with CH residents1 suggested a potential mean decrease of 55ml in PVRU following a TPTNS programme compared to the sham stimulation group, it is thus worth investigating whether this was an artefact, or whether TPTNS impacts on urinary retention in the frail older adult population. Additionally, it is important to ensure that any effect of TPTNS in reducing bladder leakage is not as a result of an increase in retained urine volume.

The *Patient Perception of Bladder Condition* (PPBC) is a single question global patient reported outcome measure of perceived bladder condition with six possible responses ranging from ‘My bladder condition does not cause me any problems at all’ to ‘My bladder condition causes me many severe problems’. It has good construct validity and responsiveness to change38 and is recommended as a global outcome measure for UI39. It is used at each time point with residents. However, it has also been adapted in this study for use by family carers (FC-PBC) and CH staff (S-PBC) to offer a perspective on how they believe the resident feels about their bladder condition.

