**ELECTRIC specific treatment related expected adverse events:**

In this trial the following related minor AEs are potentially expected:

- Transient skin redness at electrodes sites
- Minor itch at electrode sites

There are no related serious AEs expected in this trial.

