### *Assessment of Seriousness*

### The local PI / RRA / CI will make an assessment of seriousness as defined above.

### *Assessment of Relatedness (causality)*

The CI / RRA will make an assessment of whether the AE is likely to be related to research procedures according to the following definitions:

- **Related**: resulted from administration of TPTNS or sham stimulation or the outcomes data collection processes.
- **Unrelated**: where an event is not considered to have resulted from any of the research procedures.

Alternative causes such as natural history of any underlying disease, concomitant therapy, other risk factors and the temporal relationship of the event to the treatment are considered.

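### Section 7.2 decides by timing which adverse events are recorded, and whether falls, fractures and emergency admissions count as related, against the causal definition in section 7.3.3

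*Protocol*

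**What the plan says.** Protocol section 7.2 sets the general recording rule. Recorded events are "all AEs occurring during an electrical stimulation (treatment/sham) session, or while equipment is attached" to the leg, "or during data collection periods are recorded eg during questionnaire completion, interviews or 24-hour pad collections".

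Two things sit outside that window. Symptomatic urinary tract infections treated with antimicrobials count whenever they occur in the 18 weeks. Serious related events are to be recorded if they happen, with no time limit given.

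The same section then says: "Falls, fractures and emergency admissions to hospital are not considered as related AEs/SAEs during the trial period unless they occur during a treatment session". The sentence ends by adding the measurement of study outcomes as a second qualifying time.

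The list of expected related events that follows has two entries, minor itch at the electrode sites and "Transient skin redness at electrodes sites". It gives no onset time for either.

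Section 7.3.1 has the regional research assistant ask about events at each follow-up, but only those that meet the 7.2 criteria. It adds that events are also entered in the stimulation diary, which section 3.2 says staff complete after each session.

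Section 7.3.3 defines a related event as one that "resulted from administration of TPTNS or sham stimulation or the outcomes data collection processes". Assessors are told to weigh other possible causes, with timing as one consideration among several.

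**The concern.** Two rules for relatedness stand side by side. Section 7.3.3 asks what caused the event. For falls, fractures and emergency admissions, section 7.2 asks only when it happened. If 7.2 is applied first, as section 7.3.1 implies, the causal assessment never takes place for these events outside the window.

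A resident who falls on getting up shortly after the electrodes are removed is an example. The session is over and nothing is attached, so the fall is not related under 7.2, even if an assessor applying 7.3.3 would have attributed it to the stimulation. A non-serious reaction that first appears some time after removal meets no recording criterion either.

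What is at stake is the safety information that reaches oversight. Section 7.3.5 sends summaries of related serious events to the ethics committees, the funder, the steering committee and the data monitoring committee. An event ruled unrelated by timing does not enter those summaries, whichever arm it came from.

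**Working it through.** **Step 1: the window in hours.** The inputs are as follows.

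- Stimulation, section 3.1: "The full 12 session programme (a total of 6 hours) is delivered in 30 minute sessions twice weekly over a 6-week period". Check: 12 × 0.5 h = 6 h, which reproduces the protocol's figure.
- Data collections after randomisation, section 6.1: "Outcomes are measured at 6, 12 and 18 weeks post randomisation", so three, each with a 24-hour pad collection: 3 × 24 h = 72 h.
- Follow-up per resident: 18 × 7 × 24 h = 3,024 h.

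Share inside the window = (6 + 72) / 3,024 = 78 / 3,024 = 2.6%. Share outside = 97.4%.

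**Step 2: how far the reading of the window matters.**

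| Reading | Hours inside | Inside | Outside |
|---|---|---|---|
| Sessions only | 6 | 0.2% | 99.8% |
| Sessions and three pad collections | 78 | 2.6% | 97.4% |
| Adding 2 h of questionnaires per visit (assumed) | 84 | 2.8% | 97.2% |
| Adding 4 h of questionnaires per visit (assumed) | 90 | 3.0% | 97.0% |
| Sessions and pad collections, baseline included, same denominator | 102 | 3.4% | 96.6% |
| 24-hour bladder diary on a different day from each follow-up pad collection (assumed) | 150 | 5.0% | 95.0% |

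Within the six-week treatment period (6 × 7 × 24 = 1,008 h), sessions cover 6 / 1,008 = 0.6%. With the 6-week pad collection the figure is 30 / 1,008 = 3.0%.

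**Step 3: trace one event through the sections.** Take an emergency admission caused by stimulation but starting after the electrodes are off, on a day with no data collection.

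1. General rule in 7.2: not during a session, attachment or data collection, so not recordable by this route.
2. Serious related events clause in 7.2: the event is serious, so this route is open only if it is also related.
3. Timing sentence in 7.2: an emergency admission at that time is not related. The route in item 2 closes.
4. Enquiry under 7.3.1: restricted to events meeting 7.2, so the research assistant has no instruction to ask about it.
5. Definition in 7.3.3: the event is related, because it resulted from stimulation. Nothing in items 1 to 4 brings it to this assessment.

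Falls and fractures take the same path. A different serious event, such as a late serious skin injury, does not: item 3 does not apply to it, and it stays recordable under item 2.

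**Step 4: is there another source?** Falls, fractures and emergency admissions in the previous six months are collected at baseline (section 6.2). They are absent from the follow-up lists in section 6.3 and from Table 1. The Resource Use Questionnaire takes in outside care only where it arises from incontinence (sections 6.1 and 11.1).

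**The case against.** The strongest reply is that the restriction is deliberate and proportionate. Section 7.2 describes a low-risk trial with an established safety profile. Background falls and admissions will be common in frail residents, and two ethics committees reviewed the design. The version history shows that repeat measures of falls, fractures and emergency visits were removed on purpose. No objective in section 2 is a comparison of safety, and section 10.1 plans descriptive summaries only. This stands as a defence of not collecting every background event. It does not explain why an event that is caused by the stimulation should be ruled unrelated, and it leaves 7.2 and 7.3.3 in conflict.

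A reader might also infer several stronger things that the protocol does not support:

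- *That the expected skin reactions fall outside the window.* No onset time is stated. Redness or itch can begin while the electrodes are on, and a diary completed after each session may catch what is seen at removal. Only non-serious reactions first appearing later are not clearly covered.
- *That 97% of harms are missed.* The figure is calendar time for general events. Stimulation-caused events need not be spread evenly over follow-up, and the figure does not apply to treated urinary tract infections or, on the wording, to serious related events.
- *That urinary retention is lost.* Post-void residual volume is scanned at baseline and at 6, 12 and 18 weeks, partly as a check on this.
- *That deaths are uncaptured.* Section 4.7 says reasons for attrition, chiefly death, are recorded, and section 6.5 lists death among the grounds for leaving the trial.

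**Conclusion.** The contradiction is real. For falls, fractures and emergency admissions, section 7.2 fixes relatedness by timing, and that also shuts the serious related events route for those three types. Section 7.3.3 fixes relatedness by cause. As written, a stimulation-caused event of these types after electrode removal is ruled unrelated without assessment. Non-serious reactions first appearing after removal are also not clearly recordable.

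The general window covers 2.6% of the 18 weeks, and between about 3% and 5% on the wider readings. This rests on full delivery of 12 sessions, three pad collections after randomisation and complete follow-up. The number of events affected cannot be estimated, because the protocol gives no rate for falls, fractures or admissions and no onset pattern for delayed reactions. The point deserves an amendment. It does not show that the trial is unsafe or that its safety data as a whole are empty.

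**What to change.** Reconcile section 7.2, its list of expected events, section 7.3.1 and section 7.3.3 so that recording and relatedness both follow the causal definition already in 7.3.3:

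- Record any adverse event judged possibly related to stimulation or to outcome collection, whenever it occurs up to 18 weeks.
- Delete the sentence in 7.2 that classes falls, fractures and emergency admissions as not related by timing.
- Align the follow-up enquiry in 7.3.1 with the revised rule.

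The rule for treated urinary tract infections can stay as it is. The cost is a protocol amendment and a few more events to assess for causality at visits already scheduled.

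Optionally, falls, fractures and emergency admissions could be tabulated by arm from care home records for the data monitoring committee. This is more debatable: it brings back items that were deliberately dropped and means extra record extraction. The main fix does not depend on it.
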